## Methods/design

To answer the research question if EMDR is more effective in reducing symptoms of secondary traumatization in adult interpreters caused by their work in refugee care settings than in a waitlist-control group, a quasi-randomized controlled trial (RCT) with an EMDR intervention of three to six sessions will be conducted. Primary outcome is the symptom burden of secondary traumatic stress symptoms measured with questionnaire for Questionnaire for Secondary Traumatization (“Fragebogen zur Sekundären Traumatisierung,” FST) [31]. Secondary outcomes are symptom burden of PTSD due to self-experienced traumatic events (assessed with Posttraumatic Diagnostic Scale [32]), depression (PHQ-9 [33]), anxiety (GAD-7 [34]), and somatization (SSD-12 [35]) as well as quality of life (SF-12), quality of professional life (PROQOL-5 [36]), and psychological wellbeing (WHO-5 [37]). The study is conducted with the aim of improving trauma-informed care and, more specifically, expanding the knowledge of trauma-confrontation techniques in the broader context of trauma-related disorders, as these have repeatedly proven to be effective [38, 39].

### Participants and recruitment

Potential participants will be recruited in a German State registration and reception center for refugees in Heidelberg (Patrick-Henry-Village). In this initial reception center, interpreters work as professionals or on a voluntary basis in various settings, such as in social or procedural advice or in the medical field, in order to include different types of workload, intensity, and forms of care for refugees [17]. In addition, further interpreters are to be recruited in other initial reception settings and from charitable organizations. They will be contacted and informed by our study team. If they are interested, they will be invited to an initial screening appointment and informed verbally and written about the procedure of the study. If they agree to participate in the study, written informed consent will be obtained. A personal evaluation to assess inclusion and exclusion criteria will be conducted by an experienced therapist of the study team. Inclusion criteria are adult participants (≥ 18 years), working on professional or voluntary basis as interpreters in the Patrick-Henry-Village or other settings that suffer from secondary traumatic stress, verified using the Questionnaire for Secondary Traumatization and reaching the cut-off-score of ≥ 65 [31]. Exclusion criteria for participation in the study are active suicidal ideation or self-harming behavior, acute substance abuse, and psychotic symptoms. For this purpose, the respective symptoms and substance use behavior are asked about in detail during the personal interview, but no standardized tool is used. The timeline of the study design is depicted in Fig. 1. Additionally, a questionnaire-based survey with a set of different questionnaires for secondary outcomes will be conducted. These data will be assessed with an online tool. The detailed SPIRIT checklist can be viewed as an enclosed document.

**Fig. 1 Fig1:**
[figure not shown]
Timeline of the study design

### Primary outcome measure

The questionnaire-based data collection will be carried out upon the initial screening appointment (T1) for each group. For the intervention group, the second data collection point (T2) is around 6 weeks after T1, after the last session for the intervention, then 4 weeks (T3) and 8 weeks (T4) after T2. For the waitlist control group, T2 will be 6 weeks after T1, then after their last session (T3) and 4 weeks (T4) after T3. Also see Fig. 1. The participants will receive the link to the online questionnaires as well as reminders, if necessary, by email.

Secondary traumatic stress will be surveyed with the Questionnaire for Secondary Traumatization (“Fragebogen zur Sekundären Traumatisierung,” FST) [31]. This questionnaire surveys different symptoms of secondary traumatic stress based on diagnostic criteria of DSM-V for posttraumatic stress disorder, such as rumination, intrusions or nightmares, avoidance behavior, and, furthermore, cognitive or behavioral changes. The frequency of the above symptoms in the last week is assessed by 31 items on a 5-point Likert scale (1 = never, 5 = very often). From a sum score of ≥ 65, moderate secondary traumatic stress can be assumed. The structure of the questionnaire is similar to the Impact of Event Scale [40] and is designed to be used in professional context. It showed good internal consistency for the total score (Cronbach’s *α* = 0.94) in three different samples of professionals.

### Secondary outcome measure

#### Posttraumatic stress

According to current knowledge, the development of secondary traumatic stress is positively correlated with one’s own biography and the experience of traumatic event, with varying correlations [9]. For the procedure of EMDR treatment, it is important to know about traumatic events in the past and potential accompanying symptoms. Therefore, a questionnaire to assess primary traumatization (Posttraumatic Diagnostic Scale, PDS [41]) was added. The current version based on DSM-5 criteria will be used [32, 42]. The PDS-5 is a self-reporting questionnaire which measures symptoms of PTSD with 20 items on a 5-point Likert scale (0 = not at all, 4 = 6 or more times a week/severe) and is a valid and reliable measure with sensitivity of 89%, specificity of 75%, and a high internal consistency (Cronbach α = 0.92). A sum score of ≥ 36 indicates a probable diagnosis of PTSD [42].

#### Professional quality of life

Due to the related concepts to secondary traumatic stress caused by professional activity, a questionnaire for “Professional Quality of Life” will be assessed. The PROQOL-5 inquires with 30 questions factors of compassion satisfaction, compassion fatigue, symptoms of burnout, and secondary traumatic stress. On a 5-point Likert scale (0 = never, 5 = very often), participants will be asked about different experiences related to their professional work as a translator. The scale has been used in different professional contexts and shows high internal consistency for all subscales (Cronbach’s *α* = 0.90 for compassion satisfaction scale, *α* = 0.80 for the burnout scale, and *α* = 0.82 for secondary traumatic stress scale). With a mean sum score for any scale of 50 (SD: 10), a sum score ≥ 57 on any scale can give an indication of elevated strain in this area [36, 43].

#### Depression and anxiety

In a study by Živanović et al. [10] secondary traumatic stress, especially negative alteration of cognition, mood, and reactivity, was shown to influence depressive and anxiety symptomatology. Therefore, depressive symptoms will be assessed by the Patient Health Questionnaire, PHQ-9 [33]. It consists of 9 items that can be rated on a 4-point Likert scale (0 = not at all, 3 = almost every day). A score of ≥ 10 showed high sensitivity (88%) and specificity (88%) for the presence of a major depressive episode. The questionnaire shows excellent reliability (Cronbach’s α = 0.86–0.89). Anxiety symptoms will be surveyed with General Anxiety Disorder, GAD-7 [34]. It is comprised of 7 items asking for typical symptoms of generalized anxiety disorder. Equally, symptoms can be equally quantified on a 4-point Likert scale. A cut-off-value of ≥ 10 shows with high sensitivity and specificity of 0.8 likeliness of generalized anxiety disorder. Reliability is likewise excellent (Cronbach’s α = 0.92).

#### Somatic distress

To date, there is sparse data on somatic symptoms in secondary traumatic stress [44]. However, it is known that there is a high prevalence of somatic symptoms in PTSD [45] and somatic complaints are also a common symptom of burnout [46]. Therefore, a questionnaire on somatic symptoms is also collected for the present study. The scale for Somatic Symptom Disorder (SSD-12) does assess B criteria of somatic stress disorder, i.e., the perception of symptom-related thoughts, feelings, and behaviors on a scale from 0 = never to 4 = very often. A sum score value of ≥ 23 shows an increased risk of somatic stress disorder. The questionnaire shows high reliability (Cronbach’s α = 0.94) [35, 47].

#### Quality of life

Beyond the previous aspects, health-related quality of life (Short Form 12, SF-12 [48]) as well as psychological wellbeing (WHO-5 [37]) will be examined. The SF-12 questionnaire is a non-disease-specific instrument and covers 8 categories, which include questions about limitations in physical or social activities, hindrance of usual role activities due to physical or psychological problems, physical pain, general mental health, vitality, and general health perception. Two scales are used to measure physical (Physical Component Summary, PCS)) and psychological aspects (Mental Component Summary, MCS)) of health-related quality of life, which show a good internal consistency with Cronbach’s *α* = 0.89 (PCS) and *α* = 0.89 (MCS) [49, 50]. Summary scores for each scale are calculated, with an average ≥ 50 indicating a better mental or physical health than the average population and ≤ 50 indicating a worse mental or physical health than the average population. The WHO-5 is one of the most frequently used questionnaires to measure general, subjective well-being with a good internal consistency (Cronbach’s *α* = 0.80–0.92). Psychological well-being is recorded using five questions about a good mood, inner peace and relaxation, energy, ability to regenerate through sleep, and enthusiasm in the last 2 weeks. These can be agreed on a scale of 1–5 with 0 = at no time and 5 = all the time. A total score is calculated based on the number of points and multiplied by 4, with a score of 0 representing the worst and a score of 100 representing the best well-being. Used as a screening tool for depression, a sum score ≤ 50 indicates a positive screening result [37]. For the analysis of the results, the changes in the total scores or the described subscales of the primary and secondary outcomes before the intervention (T1) compared to after the intervention (T2, T3), as well as in the comparison of the intervention group with the control group, are of interest.

### Randomization

Participants will be randomly assigned in either the intervention group or waiting list control group. Because of a rather small sample size, and to ensure seamless and reliable allocation for available therapists, this will be carried out through alternating allocation of participants at the initial screening interview for the study to avoid large differences in sample size. The allocation to one of the two groups is therefore already determined before inclusion in the study. Participants will be informed verbally at the time of the initial screening interview by the responsible therapist. Blinding is neither possible for the participant (as filling out of questionnaires during waiting time), nor for the EMDR therapist, as collaborative planning is necessary for the distribution of participants, as the therapists mainly work clinically. The team of EMDR therapists available to conduct the intervention comprises of five persons. Both groups will receive the same intervention that is planned as follows. A detailed participant timeline can be found in Fig. 2.

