
### Data collection management

Data will be collected manually at the first appointment (informed consent, Questionnaire for Secondary Traumatization, information on exclusion criteria) and then via online-survey with “Unipark” [61]. Correct and accurate data collection and, if necessary, reminding of participants will be performed manually at regular intervals. No further control of data collection will be performed. Only members of the study team and colleagues of the research group have access to the dataset. Data are stored pseudonymized in a secure and accessible manner in the responsible department. Third parties do not have access to the data.

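### Open alternation at the screening interview makes the next group predictable to those who decide eligibility, so the between-group comparison is unprotected against selection bias

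*Protocol article*

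**What the plan says.** The title, abstract and Background call the trial quasi-randomized. The Randomization section opens by calling the assignment random and then explains that "this will be carried out through alternating allocation of participants at the initial screening interview". It gives two reasons: to keep group sizes similar in a small trial, and to make allocation workable for the available therapists. It adds: "The allocation to one of the two groups is therefore already determined before inclusion in the study". On disclosure it says: "Participants will be informed verbally at the time of the initial screening interview by the responsible therapist". Therapists are not blinded because "collaborative planning is necessary for the distribution of participants".

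On eligibility, Participants and recruitment says: "A personal evaluation to assess inclusion and exclusion criteria will be conducted by an experienced therapist of the study team". Inclusion requires secondary traumatic stress "verified using the Questionnaire for Secondary Traumatization and reaching the cut-off-score of ≥ 65". The exclusion criteria (suicidality or self-harm, substance abuse, psychotic symptoms) are "asked about in detail during the personal interview, but no standardized tool is used".

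On the order of measurement, Data collection management says: "Data will be collected manually at the first appointment (informed consent, Questionnaire for Secondary Traumatization, information on exclusion criteria) and then via online-survey". Primary outcome measure adds that participants receive the link to the online questionnaires by email.

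**The concern.** Strict alternation is deterministic. If the person who judges eligibility knows the coming group, the decision to exclude someone, the order of interviews and the way the study is presented can all depend on it, even without intent. Participants can also decline after hearing that they would have to wait. The two groups may then differ in ways that were not measured.

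This matters more here than in many trials. All listed outcomes are self-report questionnaires, participants and therapists know the group, the analysts are unblinded, and the control is a waiting list. Sound allocation is the main support for a causal reading of the T1–T2 contrast, which is the hypothesis stated in Background.

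A second effect concerns baseline. T1 questionnaires completed after a participant knows whether treatment starts now or later may be answered differently, and T1 is the reference for change.

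**Working it through.** **1. Who knows what, and when.** Setting the sections side by side:
- The group follows a fixed alternating sequence and is settled before inclusion (Randomization).
- Consent, the FST and the exclusion questions belong to the first appointment (Data collection management).
- A therapist of the study team judges eligibility (Participants and recruitment).
- A therapist announces the group at that interview, and the five EMDR therapists plan the distribution jointly (Randomization).

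The text does not say outright that the screening therapist knows the previous allocation. It follows from open alternation, joint planning and disclosure by the therapist. No step hides the sequence.

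**2. Predictability of the next allocation.** The guesser knows earlier allocations, does not know block sizes, and picks the group that is behind.
- Alternation: 100%.
- Blocks of 2: (0.5 + 1)/2 = 75%.
- Blocks of 4: (0.5 + 2/3 + 2/3 + 1)/4 = 71%.
- Blocks of 2 and 4 chosen equally often: one third of participants fall in blocks of 2 and two thirds in blocks of 4, so 0.75/3 + 0.708 × 2/3 = 72%.
- Varying blocks of 4 and 6: 69%; of 4, 6 and 8: 68% (simulation, 40 participants).
- Simple randomization: 50%.

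**3. The plan's sample size.** Statistical analyses gives d = 0.5, α = 0.05, power 0.8, n = 34, raised to 40. A repeated-measures ANOVA interaction with f = 0.25, two groups, two measurements and correlation 0.5 (the last two are my assumptions) gives N = 34 with power 0.807. For dropout, 34 × 1.18 = 40.1, while 34/0.82 = 41.5, that is 42; the stated 40 is close. None of this depends on the allocation method. The target of 40 gives 20 per group.

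**4. What a prognostic shift would do (illustration).** The size of shift b, in SD, is an assumption. For a simple two-sided comparison of two means with n = 20 per group, the noncentrality is b/√(2/20) = b/0.316, and type I error = Φ(b/0.316 − 1.96) + Φ(−b/0.316 − 1.96).

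| Assumed shift b | Share of d = 0.5 | Type I error |
|---|---|---|
| 0.1 | 20% | 6.2% |
| 0.2 | 40% | 9.7% |
| 0.3 | 60% | 15.8% |

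With 17 per group the figures are 6.0%, 9.0% and 14.1%.

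**5. Group sizes.** The sequence runs over people interviewed, so anyone not included uses up a place. Simulated results at 40 included (inclusion rates are assumptions):

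| Inclusion rate | Difference ≥ 4 | Difference ≥ 8 |
|---|---|---|
| 100% in both groups | 0% | 0% |
| 90% in both groups | 14% | 0.1% |
| 80% in both groups | 29% | 1.7% |
| 50% in both groups | 50% | 12% |
| Simple randomization, for comparison | 63% | 27% |

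If inclusion depended on the known group (90% against 70%), the mean difference would be 5.5, and 81% of trials would differ by 4 or more. An uneven split alone costs little: 24/16 is worth 4 × 24 × 16/40 = 38.4 participants in equal groups, a loss of 1.6/40 = 4%.

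**6. Order of disclosure and T1.** The online battery comes after the manually collected items and is reached by an emailed link, while the group is announced at the interview. Completion after disclosure is therefore the likely order for the online secondary measures. The FST is taken at the first appointment, and nothing says whether that is before or after the announcement. The timeline figures were not available for this check.

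**The case against.** The authors disclose the design: the title says quasi-randomized, and the Randomization section gives a practical reason, since the five therapists work mainly in clinical care. The FST threshold of 65 limits discretion on inclusion. Statistical analyses plans a baseline comparison, including FST load and PTSD symptoms, and covariates for psychiatric treatment, medication and personal trauma. It also compares the waiting group's own waiting and treatment periods, a contrast that does not depend on who was steered to which group. Participants cannot be blinded, so later self-reports are made with the group known under any method.

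Much of this stands as mitigation, but it does not remove the point. The label discloses the weakness without curing it, and it conflicts with the wording on random assignment in Randomization, on randomized participants in Statistical analyses and on randomization in Ethics and dissemination. The FST threshold does not govern the exclusions. Baseline checks and covariates address only what is measured. The within-person contrast is a before–after comparison, not the stated comparison with waitlist.

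Three stronger readings are tempting but unsupported:
- **Bias is certain, or allocation is the only protection.** The document shows an unprotected risk and some partial mitigation.
- **Serious imbalance in group size is likely.** A reader might take the 21% prevalence in Background as the eligible share, so that 40/0.21 ≈ 190 people are alternated; the hypergeometric chance of 24/16 or worse is then 0.213. That prevalence describes a sample of interpreters, not people who came forward for screening, and such a split costs only about 4%.
- **All baseline values are distorted.** For the FST the order is unstated. For the online measures the order is an inference, and neither direction nor size of any effect is known.

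**Conclusion.** The point holds as a defect in how allocation is fixed. Alternation is open, settled before inclusion, announced at the interview that decides eligibility, and elsewhere called random. Given knowledge of the previous allocation, predictability is 100%, and the T1–T2 between-group comparison is unprotected against selection; the planned analyses mitigate this only in part. How much bias would follow cannot be derived from the document. The error rates of 6% to 16% rest on assumed shifts of 0.1 to 0.3 SD and a simple two-group test, not on the planned growth model. Reporting of baseline with the group known is likely for the online secondary measures and only possible for the T1 FST. Unequal group sizes are a minor point.

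**What to change.** For all participants not yet allocated, use a computer-generated 1:1 list with randomly varying, undisclosed block sizes, for example 4 and 6. Someone who does not interview, such as the supporting biostatistician, should hold it. Open each assignment only after consent, confirmed eligibility, the T1 FST and submission of the T1 online battery. Blocks of 4 and 6 keep the group difference at 3 or less at any time (half the largest block) and so meet the aim of similar sizes. They remain about 69% guessable to someone who tracks all past allocations, which is why opening after eligibility is essential. Flag participants already alternated.

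Cost: a formal ethics amendment, to be examined before implementation as Ethics and dissemination provides, and slightly later knowledge of the group for therapists and participants. The sample size does not change.

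One participant had been included at submission, but Trial status expected recruitment to end around June 2024 and the article appeared in October 2024. If recruitment is complete:
- describe the trial throughout as quasi-randomized with unconcealed alternation;
- remove the wording on random assignment and randomized participants;
- report numbers screened, excluded and declining by assigned group;
- limit causal conclusions accordingly.

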**Fig. 2 Fig2:**
[figure not shown]
Participant timeline

### Intervention

Participants will be allocated to a therapist, medical doctor or psychologist of the department who will have completed, at least, EMDR training level 1. The EMDR treatment that will be carried out is comprised of 8 phases according to Shapiro [51]. In the first session, phases 1 and 2 will be conducted. The first phase includes the establishment of a therapeutic relationship as well as the exploration of the symptomatology and the trauma history. In this case, the therapist will comprehensively examine the symptoms of secondary traumatization including distressing situations relating to their work in refugee care in the present. Emotion regulation strategies of the participant will be elaborated. With help of the “adaptive information processing” model (AIP), the therapist and the participant will work out underlying stress situations from the professional context. According to the AIP model, traumatic memories, but also other “live events” or disturbing experiences that do not accord to the trauma criteria, can create a “pathogenetic memory.” These pathogenetic memories are stored in a dysfunctional way, are not connected to adaptive memory networks, and, subsequently, cause symptoms. Based on this assumption, repeated exposure to details of refugees’ traumatic experiences leads to dysfunctional storage of this experience of the affected interpreters [52, 53]. The therapist and the participant will carve out the respective distressing situations and classify them on a scale from 0 to 10 (subjective level of disturbance, SUD), as stated in the EMDR manual. Additionally, the participant will be introduced to the EMDR technique itself. An imaginative exercise, “safe place,” will be executed together and reinforced with EMDR technique. Techniques to stop flashbacks will be discussed. Additionally, the participant will receive a further imagination exercise, called “safe exercise,” that helps distancing oneself from disturbing thoughts. The first session takes 50–60 min. Phase 3–7 will be conducted in the following sessions according to the EMDR standard protocol. Phase 8 will be performed at the beginning of every exposition session. The EMDR standard protocol will be applied. This means that the disturbing memories will be worked on in a specific (“the first, the worst, the last”). However, by mutual agreement, the order in which the stressful memories are processed is left open to the therapist and the participant, if this leads to greater openness to therapy and adherence. Sessions will take place once a week; the therapist and participant will agree mutually on the date of the sessions, and they can be adapted to the participants’ needs. The confrontational sessions ends ideally when the SUD is 0. However, depending of the processed content, this cannot always be achieved, for example if the participant processes earlier stressful memories through so-called affect bridges. In this case, the session can be closed if SUD is not 0 but only reduced from the initial level. In this case, work on this memory will continue in the following session (phase 8). The processing time can differ between patients and takes around 60–90 min. A maximum of six sessions will be conducted. The number of sessions will be adapted to the participants needs. This implies that within the span of these six sessions, the stressful situations related to the participant’s work with refugees, which the participant seeks to address, are systematically managed. If a complete reduction of the SUD is not achieved within a single session, the issue may be resolved over 2–3 sessions. However, it is generally expected that each session is self-contained, as the nature of the underlying stressors suggests that a full reduction in SUD can be accomplished within one session. Consequently, the number of sessions corresponds to the number of specific situations requiring attention. Conducting fewer than six sessions does not imply that any therapeutic content is omitted. Participants in both groups receive the same intervention.
